### Statistical methods

The trial analysis will follow the intention-to-treat principle, as such all participants who were randomized (n = 400) will be included regardless of their adherence to the study. After initial descriptive and graphical examination of the response measurements (with a consideration of transformation), we will examine correlations among markers within each of the hypothesized pathways that are being examined between physical activity and breast cancer risk. This approach will guide us to a hypothesis-driven pathway-based evaluation of intervention effects. Specifically, the correlation analysis will explore if consistent patterns supportive of a simultaneous evaluation of multiple markers in each pathway is warranted. As a formal evaluation approach, we will apply the linear mixed effects model methodology to compare the changes from the baseline to 12-month follow-up in levels of estrogens, markers of obesity, insulin resistance and inflammation and also in our psychosocial outcomes of interest. The mixed model evaluation will be considered for both individual markers (univariate outcomes) and pathway-based multiple markers (multivariate outcomes), of which we propose the latter to be our primary evaluation scheme.

The analysis will be performed with and without covariate adjustments, initially without any adjustment based on the randomized design, followed by adjustment for covariates in which substantial imbalances between the two groups were observed. Rates of recruitment and adherence to the intervention as well as maintenance of exercise behaviour will be estimated and examined in association with the study participant characteristics.

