### Randomization

Randomization was stratified by study centre (Edmonton or Calgary) and baseline BMI (< or ≥30) to ensure balance between the two arms with respect to study sites (i.e., potential differences in the participant populations) and the proportion of obese participants. Blocking was used within strata with blocks of four or six to ensure balance between the two arms with respect to the number of participants. The use of different blocks sizes that we randomly permuted made it harder to predict the sequence that was up-coming. The random allocation sequence was generated by user-defined functions in R software (version 2.11). The allocations were concealed in numbered envelopes prepared by a staff member unrelated to the study team. Randomization was performed only for women who were eligible for the study and had completed all baseline measurements (Figure 
1). Each participant was randomly assigned to either the HIGH volume (300 minutes/week) aerobic exercise intervention group or to the MODERATE volume (150 minutes/week) aerobic exercise control group. Participants and exercise trainers, by necessity, were unblinded to the intervention assignment.

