#### Health-related fitness assessments

Only participants who successfully passed the baseline blood screening criteria were invited for health-related fitness assessments (Figure 
1) that included resting heart rate and blood pressure assessment, a submaximal fitness test, anthropometric and body composition measurements. All fitness assessments were performed by a Canadian Society for Exercise Physiology Certified Exercise Physiologist (CSEP:CEP®) and one assistant exercise trainer. The same testing protocols and equipment were used at the Edmonton and Calgary study centers and all measurements were taken at baseline and at 12 and 24 months.

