##### Body composition/Anthropometry

Anthropometric data on standing height, weight, waist and hip circumference were measured using standardized methods and equipment at the time of the fitness tests. Waist circumference was measured using the National Institutes of Health protocol and hip circumference was measured using the World Health Organization procedure with an anthropometric measuring tape
[64]. Full body dual energy X-ray absorptiometry (DXA) scans were taken using a Hologic DXA system in Calgary and a General Electric Lunar iDXA in Edmonton to assess overall percent body fat, total lean body mass, total fat mass and bone mineral density. Computed tomography (CT) scans were taken at the level of the umbilicus to measure subcutaneous and intra-abdominal adiposity. Three single slices were taken at the L5 vertebrae and these data were then transferred to our study radiologist at the Cross Cancer Institute in Edmonton who reviewed each scan individually using a software program (Aquarius Intuition by Terarecon, Inc.) that was used to quantify amount of subcutaneous and intra-abdominal fat at this level of the abdomen. Because of the high cost associated with both the DXA and CT scans, only participants who had completed all screening stages and considered eligible for the study were given these scans at baseline. These assessments were repeated 12 months and 24 months later (Table 
3).

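### The rule of adjusting only for observed imbalance in effect keeps centre and BMI stratum out of the model, does not carry over the baseline adjustment used for sizing, and lets chance choose the second model

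*Protocol article*

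**What the plan says.** In the protocol article, Statistical methods describes the formal analysis this way: "we will apply the linear mixed effects model methodology to compare the changes from the baseline to 12-month follow-up". On covariates it sets an order: "initially without any adjustment based on the randomized design", then "followed by adjustment for covariates in which substantial imbalances between the two groups were observed". It gives no covariate list and no threshold for a substantial imbalance, and it does not label one of the two results as primary.

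The Randomization section says: "Randomization was stratified by study centre (Edmonton or Calgary) and baseline BMI (< or ≥30"), and "Blocking was used within strata with blocks of four or six". Its stated purpose is to balance the arms on site and on the proportion of obese women. No section places either factor in an analysis model. The only covariate named elsewhere for possible adjustment is diet (Dietary habits).

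The Sample size section bases the calculation on 12-month means on the log scale, adjusted for baseline.

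A side point concerns centre. Health-related fitness assessments, which counts body composition among its measurements, says: "The same testing protocols and equipment were used at the Edmonton and Calgary study centers". Body composition/Anthropometry says DXA scans were made "using a Hologic DXA system in Calgary and a General Electric Lunar iDXA in Edmonton".

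**The concern.** The article states this rule outright, so it is not a detail left to a separate analysis plan. It works against the design in three ways.

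- **Strata.** Stratified blocking removes imbalance in centre and BMI stratum. A trigger that responds only to imbalance therefore passes over the two factors that the design itself treats as important. A standard error that ignores balanced prognostic strata is too large.
- **Chance selection.** Among covariates that were not stratified, those selected are the ones that happen to differ between arms, whatever their prognostic value. The second model cannot be written down before the data are seen.
- **Baseline value.** The trial was sized on a baseline-adjusted comparison, but the analysis begins unadjusted. If change is compared without a baseline covariate, the analysis is less precise than the one used for sizing.

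At stake are precision and the transparency of the adjusted result.

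**Working it through.** **Inputs from the article.** Two-sided α 0.05; 150 per group for 80% power to detect a 12% change (Sample size); 400 randomised in total (Trial overview, Statistical methods), taken here as 200 per arm; four strata (2 centres × 2 BMI classes) with blocks of four or six (Randomization). Sample size also contains the phrase 400 per group, which conflicts with the total of 400; that is a separate matter.

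**Assumed, not in the article.** The share R² of outcome variance explained by the strata, the baseline to 12-month correlation ρ, and p<0.05 as the meaning of substantial.

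**1. The plan's own figure.** No SD is given, so 150 per group cannot be checked independently. Solving δ = (1.960 + 0.842) × SD × √(2/150) gives SD 0.350 for δ = ln 1.12 (increase) and 0.395 for δ = −ln 0.88 (decrease). The standardised signal is 2.802 at 150 per arm and 2.802 × √(200/150) = 3.235 at 200 per arm, where power is Φ(3.235 − 1.960) = 89.9%.

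**2. Would the rule select the strata?** In null simulations (4,000 runs at each of three values of R², n = 400, equal centres, 40% with BMI ≥30), the standardised difference between arms for centre or BMI stratum never exceeded about 0.04, and neither was flagged in any run. With ten other independent covariates, the chance that at least one is flagged is 1 − 0.95^10 = 40% (simulated 39–41%).

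**3. Size of the test that ignores the strata.** With balanced strata, the true standard error is √(1 − R²) times the one used, so the size is 2 × [1 − Φ(1.960/√(1 − R²))]:

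| R² of analysed outcome | 1.960/√(1−R²) | Size |
|---|---|---|
| 10% | 2.066 | 3.9% |
| 20% | 2.191 | 2.8% |
| 30% | 2.343 | 1.9% |

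The simulations gave 3.8, 2.6 and 1.8%. With the strata in the model they gave 4.4–4.8%.

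**4. Power at 200 per arm.** Ignoring the strata, power is Φ((3.235 − 1.960)/√(1 − R²)); including them, it is Φ(3.235/√(1 − R²) − 1.960).

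| R² | Strata ignored | Strata included |
|---|---|---|
| 10% | 91.1% | 92.6% |
| 20% | 92.3% | 95.1% |
| 30% | 93.6% | 97.2% |

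The cost is 1.5 to 3.6 percentage points.

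**5. The same for change scores.** A stratum effect that is equal at baseline and 12 months cancels in the change, so R² for change is 0 and the size is 5%. A simulation of this case (4,000 runs per setting, ρ = 0.6 within strata, strata explaining 10, 20 or 30% of levels) gave 5.0, 4.8 and 5.5% for change, with Monte Carlo error about 0.3 points. Only strata that predict the change itself bring back the loss in steps 3 and 4.

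**6. Baseline value.** With equal variance σ² at both times, an unadjusted change has variance 2σ²(1 − ρ) and a baseline-adjusted comparison has σ²(1 − ρ²). The ratio is 2/(1 + ρ).

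| ρ | Ratio | Power at 200 per arm, change without baseline |
|---|---|---|
| 0.5 | 1.33 | Φ(3.235/√1.333 − 1.960) = 80.0% |
| 0.8 | 1.11 | Φ(3.235/√1.111 − 1.960) = 86.6% |

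Both compare with 89.9% when baseline is adjusted for. At ρ = 0.5 the loss equals the whole gain from 150 to 200 per arm, since 200/1.333 = 150.

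These are calculations for one marker at a time. The article's primary scheme is multivariate by pathway, so they indicate the order of size only.

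**The case against.** The strongest reply is that the planned analysis compares changes. Stable centre and BMI effects then largely cancel, as does a constant offset between DXA machines. That stands: the sizes in step 3 apply only if the strata explain that share of whatever is analysed, and for change the share is probably smaller.

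It can also be said that comparing changes already uses baseline. That is only partly right. Subtracting baseline is not the same as adjusting for it, as step 6 shows. A mixed model that constrains the arms to a common baseline mean would recover most of that precision, but the article does not say that its model does so.

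The order of the two analyses suggests that the unadjusted result leads and the adjusted one supports it. That is a fair reading, though neither is labelled. Diet may be considered independently of the imbalance rule, so the rule need not be the only way into the model; no such route is given for centre or BMI stratum.

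A reader might infer more than the article supports:

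- **Bias.** Omitting balanced strata does not bias the randomised comparison.
- **Inflated type I error from having two results.** Nothing says that the more favourable result will be reported. In the simulations of step 2, rejecting when either test was significant gave 4.0, 2.8 and 2.0%. The figure moves to either side of 5% with the set-up assumed, so no inflation can be claimed.
- **Information lost in proportion to R².** Stratified blocking already makes the estimate precise. Only its standard error is overstated, so the loss is that in step 4.
- **DXA outcomes undermined by two machines.** Each centre contributes to both arms and the devices are disclosed. Only a difference in scale or variance would remain in change scores, and only for DXA outcomes.

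**Conclusion.** The point holds as one of efficiency and transparency. The stated rule will in practice leave out centre and BMI stratum, may bring in other covariates by chance, and does not explicitly keep the baseline adjustment on which the trial was sized.

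The effect of omitting the strata is conservative: a size of 3.9 to 1.9% and 1.5 to 3.6 points of power if they explain 10 to 30% of the analysed outcome, and close to nothing if their effects are stable over time. The baseline value may matter more: a variance ratio of 1.33 to 1.11 for ρ of 0.5 to 0.8, provided the model really compares change with no baseline term or constraint. The article gives neither R² nor ρ, so these are ranges under assumption.

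The equipment statement conflicts with the DXA description, because body composition is listed among the assessments that it covers. This is a minor correction of wording and carries no weight in the main conclusion.

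**What to change.** - In Statistical methods, replace the imbalance rule with a primary mixed model that contains, for every outcome, centre, BMI stratum (<30/≥30) and the baseline value of that outcome, fixed in advance.
- Keep the unadjusted analysis and any imbalance-driven adjustment, both labelled as sensitivity analyses.
- In Health-related fitness assessments, except DXA from the statement about common equipment, so that it agrees with Body composition/Anthropometry.

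The cost is wording only. Centre and BMI stratum were recorded for randomisation, and the baseline values are in the data collection schedule. The article describes the blood assays as still to be done, so for those markers the model can be fixed before results exist.

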## Discussion

The primary results from BETA Trial will be central for determining if 300 minutes/week of vigorous intensity aerobic exercise is better than 150 minutes/week for postmenopausal breast cancer risk reduction. Furthermore, any dose–response effects that are found between exercise dose and blood biomarker changes will help to strengthen (or refute) current hypotheses surrounding the biologic mechanisms underlying the association, which remain unclear. Yet the value of the BETA Trial findings depends, first and foremost, on the quality of our study design and data collection methods.

The design of the BETA Trial was informed in large part from our previous experience with the ALPHA Trial in which we found that aerobic exercise influenced several biomarkers associated with breast cancer risk. In addition, we noted a possible dose–response effect between increasing adherence to the exercise intervention and corresponding changes in biomarker levels. Since these comparisons were made within an allocation arm of a trial, rather than from a true randomized comparison, the BETA Trial was necessary to confirm these dose–response effects with prescribed aerobic exercise.

Based on the experience of the ALPHA Trial, we recognized that women willing to participate in an exercise intervention trial strongly preferred being randomized to an exercise group rather than a control group that did no exercise. Furthermore, there was some contamination within the control group of the ALPHA Trial with some study participants starting an exercise and weight loss program on their own. Amongst the control group, 53% started exercising and 63% decreased their caloric intake over the year based on self-report as compared to their baseline assessments of the past 12 months. Given that the relevant research question after the ALPHA Trial was “what is the optimal dose of aerobic activity?” rather than “does exercise influence these biomarkers for breast cancer?”, we opted for a dose–response trial.

Several aspects of the BETA Trial design, including subject recruitment, data collection methods, exercise intervention, sample size and analysis also derived from our experience with the ALPHA Trial. The ALPHA Trial had very high retention and adherence rates and provided meaningful insights into the potential etiology between physical activity and breast cancer risk. Hence, for the BETA Trial, we used the same study methods with some refinements. For example, we recognized the advantage of media campaigns for recruitment and so used these effectively once we had all protocols in place and had begun recruitment through letters of invitation with the breast screening program. The media campaigns provided a large influx of possible participants all at once which demanded an increase in study personnel to meet this recruitment drive. In addition, we created and used a study website more routinely to communicate with our study participants. We also enhanced our newsletters by making them longer, with more information and articles to interest the participants. In the ALPHA Trial, we used group sessions offered every three to four months in addition to individual exercise sessions whereas in the BETA Trial, group exercise sessions were offered every month. We also increased the number of exercise trainers and the facilities were open six days/week with availability 12 hours daily for participants to drop in. In the BETA Trial, we continued the use of several incentives plus additional incentives to enhance adherence, e.g., adherence challenges.

A key component to the success of a multi-centered trial, such as this one, is standardization of all study methods across study sites. Hence, we developed standardized protocols for all of the study methods and a lengthy manual of operations. We held weekly meetings of all team members at both sites that included the exercise testers, study staff and the two principal investigators. In addition, our study staff and exercise testers met throughout the study to ensure that the methods for exercise testing, for delivering the exercise intervention, and for collecting and managing all the data were standardized. Any changes to study procedures or protocols that were needed were fully discussed and implemented at both sites. Several additional factors were crucial to the success of our study. The BETA Trial methods had been largely developed and tested in the ALPHA Trial and therefore we were able to learn from our successes and build upon them to deliver an even better intervention to a larger study population. Recruitment to the study was greater than expected partly because of the heightened awareness of our research activities due to previous publicity from the ALPHA Trial. Also retention to the study was very high in (96%) since we implemented protocols to follow-up our non-adherent participants and provided participants with a number of incentives and feedback on their progress - e.g., receiving results from their health-related fitness and body composition measurements at 12 and 24 months - to help maintain involvement in the trial. We had preliminary evidence from the ALPHA Trial that previously inactive, postmenopausal women could be motivated to achieve and sustain high levels of activity and hence used all of our previously developed approaches, and several new incentives that were outlined above, to achieve exercise adherence even with the HIGH volume group. Another strength of our study was the use of rigorous measurement methods for all of the assessments made, including objective assessments of physical fitness, physical activity, sedentary behaviour and body composition. Our laboratory assays are being conducted in highly reputable laboratories (of co-author [name]) employing methods that provide accurate and reliable measurements.

The implications of the BETA Trial findings are diverse. By prescribing a higher dose of exercise than in previous, comparable biomarker trials
[10, 24, 33, 75, 76], the BETA Trial will reveal whether or not greater reductions in proposed biomarkers for breast cancer are possible with additional exercise. Furthermore, further exploration of the mechanisms underlying biomarker changes - e.g., the potential benefit from exercise in the absence of significant weight loss - will enable clearer public health messaging for primary cancer prevention. Our secondary outcomes from the trial, including quality of life, perceived stress, sleep, and happiness, could help motivate inactive women to become physically active after menopause. Furthermore, the BETA Trial will inform future disease prevention initiatives by demonstrating the ability of these women to *achieve* a high volume of regular exercise over the long-term and to *maintain* this level of activity independently, 12 months beyond the intervention period. Ultimately our findings will help to refine and strengthen the current public health guidelines for primary breast cancer prevention, to decrease the future incidence of breast cancer.
